### 2.5. Experimental Protocol

The first visit is an inclusion visit, where the examining physician will perform the neurologic exam, and verify the inclusion and exclusion criteria. Patients will obtain information regarding the protocol, consent form, and the other questionnaires to be filled. They will be called in the following days to check if he/she agrees to participate in the study and therefore to plan the stimulation sessions. In case of acceptance, an appointment will be scheduled in order to sign the consent form and deliver a booklet containing the VAS for pain to be filled for one week prior to the stimulation week and during the week of stimulation. If present, medications and physical therapy will be kept the same as the previous month. Patients will be asked to restrict stimulant consumptions (e.g., caffeine, nicotine) at least three hours prior to their appointments.

Each patient will be randomly assigned to receive 3 blocks separated by a washout interval of three weeks (anodal tDCS over M1 contralateral to the most affected hand, cathodal tDCS over the cerebellum, and sham over either cortical site). Each block will consist of five 20-min stimulation sessions, applied on day 1 to day 5 (D1 to D5). On D1, dexterity will be quantified based on the time required to perform the 9-HPT. Each patient will be evaluated for fatigue (MFIS), anxiety and depression (HADS), spasticity (MAS), motor power (MRC), and cerebellar function (ataxia scale). Afterwards, tDCS will be performed in a quiet and well-illuminated room with the patient sitting in an armchair without any concurrent cognitive or motor task. The stimulation session will be repeated from D1 to D5. At the end of D5 session, each patient will undergo the same evaluation as done on D1 (9-HPT, MFIS, HADS, MAS, MRC, ataxia scale), as well as the CRQ, CGI, and will be delivered a VAS booklet (pain) to be filled for one week following D5 and for one week prior to the next tDCS block. 

Each patient will be included in the study for 3 months. 2 patients per week will undergo the stimulation block. The study will take place for a total duration of 12 months, and the final data analysis will be performed in less than a year. The schematic diagram of the protocol is illustrated in Figure 3. 

### 2.6. Patient Withdrawal, Risks and Benefits

No available conditions in the study protocol can be expected to trigger patient’s withdrawal. However, any patient can withdraw consent at any point during the study without any consequences. The side effects related to tDCS are minimal to none. Mild skin irritation has been rarely reported and can be avoided by dipping the stimulating electrodes in a saline solution before installation. Protocols of tDCS have been the subject of many studies with no serious side effects described to date. A well-experienced team will be in charge of performing tDCS. This study is designed to improve knowledge regarding tDCS in MS patients with altered dexterity and cannot provide direct or lasting medical benefit, but the obtained results might serve in guiding the therapeutic use of tDCS in this domain.

### 2.7. Data Management

The study records will be kept as confidential as possible. Patients’ information will be carefully collected. What is learnt from the data will be described only in a way that does not identify patients. To protect the patients’ privacy, data will be linked to a secret code. Names will be recorded only on the informed consent forms. The secret codes will be kept in a locked file and can only be accessed by the principal investigator of the study and the authorized personnel. However, study records may be reviewed by the Committee of Human Subjects in Research at the Lebanese American University. The records will be monitored and may be audited without violating confidentiality. The results of this study may be published without breaching patients’ confidentiality at any point.

### 2.8. Safety and Adverse Event Reporting

Safety measures have been well proven by Nitsche et al. In fact, the authors demonstrated that tDCS does not cause heating effects under the electrodes and does not elevate the serum neuron-specific enolase level [30,31,33], a sensitive marker of neuronal damage [66]. It does not result in changes of diffusion-weighted or contrast-enhanced MRI, or of pathological electroencephalographic patterns [33]. These protocols were tested in more than 3000 subjects worldwide with no serious adverse events (SAEs), except for some adverse events (AEs) consisting of slight itching under the electrode, mild redness attributed to neutrally driven vasodilation and seldom-occurring headache, fatigue, and/or nausea [32,35]. tDCS was studied in the context of MS, and its efficacy and safety were reported in the context of neuropathic pain [67,68], tactile sensory deficit [69], and fatigue [40,51,70,71,72,73,74,75], to cite a few. Based on the above, we believe that this study design (5 consecutive daily sessions, 20 min per session, and current intensity of 2 mA, with the proposed circuit setup) is safe and harmless.

The investigators are in charge of recording and reporting all the SAEs that might happen throughout the entire research protocol from the time of obtaining consent and throughout the whole period required to monitor the participants. SAEs will be recorded on a comprehensive form provided for this purpose. This form will be completed, printed, dated, signed, and the principal investigator will be promptly notified. Moreover, regardless of the time of onset following the protocol, all the SAEs suspected to be the result of the research protocol should be reported to the investigator when no other reasonable explanation exists. All the other AEs will be reported only on the medical card of each patient and will include the date of onset, characteristics, intensity, duration, etiologies, taken actions, treatments, and resolutions, if any. There are no specific safety measures related to this research and no important safety data to be collected.

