## Abstract

Background: Cerebellar and motor tracts are frequently impaired in multiple sclerosis (MS). Altered hand dexterity constitutes a challenge in clinical practice, since medical treatment shows very limited benefits in this domain. Cerebellar control is made via several cerebellocortical pathways, of which the most studied one links the cerebellum to the contralateral motor cortex via the contralateral ventro-intermediate nucleus of the thalamus influencing the corticospinal outputs. Modulating the activity of the cerebellum or of the motor cortex could be of help. Method: The main interest here is to evaluate the efficacy of transcranial direct current stimulation (tDCS), a noninvasive brain stimulation technique, in treating altered dexterity in MS. Forty-eight patients will be recruited in a randomized, double-blind, sham-controlled, and crossover study. They will randomly undergo one of the three interventions: anodal tDCS over the primary motor area, cathodal tDCS over the cerebellum, or sham. Each block consists of five consecutive daily sessions with direct current (2 mA), lasting 20 min each. The primary outcome will be the improvement in manual dexterity according to the change in the time required to complete the nine-hole pegboard task. Secondary outcomes will include fatigue, pain, spasticity, and mood. Patients’ safety and satisfaction will be rated. Discussion: Due to its cost-effective, safe, and easy-to-use profile, motor or cerebellar tDCS may constitute a potential tool that might improve dexterity in MS patients and therefore ameliorate their quality of life.

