#### 2.4.2. Secondary outcomes

Fatigue will be assessed using the 21-item Modified Fatigue Impact Scale (MFIS), which is relatively short, robust, and reliable [64]. It contains three subscales: cognitive (10 items), physical (9 items), and psychosocial fatigue (2 items). The items are scored from 0 to 4 (0 = Never, 1 = Rarely, 2 = Sometimes, 3 = Often, 4 = Almost always), and respondents are asked to consider their experiences with fatigue during the past four weeks.

Pain will be evaluated using a 0-10 visual analog scale (VAS) for pain. Anxiety and depressive symptoms will be assessed using the Hospital Anxiety and Depression Scale (HADS) [65]. Spasticity, motor power, and cerebellar function will be evaluated using the MAS [44], MRC [43], and ataxia scale scores [45], respectively. The MAS grading will be performed for the three upper limb segments (shoulder adductor, elbow flexor, wrist flexor), obtaining scores that can range from 0 (no increase in muscle tone) to 4 (affected parts rigid in flexion or extension) [44]. The Clinical Global Impression (CGI) and the Comfort Rating Questionnaire (CRQ) will be used to assess patients’ clinical impression and potential side effects [35]. The CRQ evaluates possible side effects (pain perception, tingling, burning, fatigue, nervousness, disturbed concentration, disturbed visual perception, and headache) observed before, during, and 24 hours after stimulation on a 10-point Likert scale. In addition, it contains two dichotomous questions that assess sleep disturbance and phosphene perception during/after stimulation. At the end of the last session of each stimulation block, patients will be asked to guess the type of stimulation to assess for effective blinding (active/sham).

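### Section 2.8 keeps non-serious adverse events on the medical card and says no important safety data are collected, so events outside the Comfort Rating Questionnaire have no stated route into the study data

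*Protocol article*

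**What the plan says.** Section 2.8 sets up two recording routes. For serious events, "SAEs will be recorded on a comprehensive form provided for this purpose", and the principal investigator is notified promptly. For the rest, "All the other AEs will be reported only on the medical card of each patient". The card entry is detailed: it "will include the date of onset, characteristics, intensity, duration, etiologies, taken actions, treatments, and resolutions, if any". The section closes with: "There are no specific safety measures related to this research and no important safety data to be collected".

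Elsewhere the protocol treats safety and tolerability as something to be measured. The abstract says that patients' "safety and satisfaction will be rated". Section 2.4.2 lists the CRQ among the secondary outcomes. It rates "pain perception, tingling, burning, fatigue, nervousness, disturbed concentration, disturbed visual perception, and headache" on a 10-point scale before, during and 24 hours after stimulation, and has two yes/no items on sleep disturbance and phosphenes. Section 2.5 places the CRQ in the evaluation at the end of the day 5 session of each block. Section 2.9 analyses secondary outcomes in the same way as the primary, across the three stimulation conditions.

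**The concern.** Two things are wrong in 2.8.

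First, its closing sentence contradicts the abstract, 2.4.2 and the SAE form described in the same section. All three commit the trial to collecting safety or tolerability data.

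Second, the word "only" in the rule for non-serious AEs names the medical card as the sole place of record. The protocol gives no step by which a card entry reaches the study dataset. The CRQ covers part of this ground, but not all the events the protocol itself anticipates and not all of the follow-up.

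At stake is what the trial can say about tolerability. A sham-controlled crossover is well placed to compare mild events between active and sham stimulation within the same patients. Followed literally, the plan would allow a statement that tDCS was well tolerated while some of the local effects the protocol attributes to it had not been counted by condition.

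**Working it through.** No figure in the plan has to be reproduced. The check sets the sections side by side.

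**1. Item coverage.** Section 2.8 names five mild events seen with tDCS. Against the CRQ list in 2.4.2:

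| Event named in 2.8 | CRQ item in 2.4.2? | Stated place of record |
|---|---|---|
| Itching under the electrode | No | Medical card |
| Redness | No | Medical card |
| Headache | Yes | CRQ, once per block |
| Fatigue | Yes | CRQ, once per block |
| Nausea | No | Medical card |

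The CRQ covers 2 of 5, and 3 of 5 are left to the card. Tingling and burning are the nearest CRQ items to itching, but they are sensations and record neither visible redness nor nausea. Section 2.6 also says "Mild skin irritation has been rarely reported". This may be the same thing as itching or redness, so it is not counted as a further missing item.

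**2. Time coverage.** The CRQ is completed at the end of day 5 and reaches to 24 hours after stimulation. At the moment 2.5 gives for completion, the 24 hours after the fifth session have not yet passed. Blocks are separated by three weeks (21 days). In that interval the pain booklet covers pain for the week after day 5 and the week before the next block. No other non-serious event has a stated record apart from the card.

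**3. Patients who leave before day 5.** Section 2.3 allows for dropout of up to 25%. Applied to 48 patients as an assumption, this is 0.25 × 48 = 12. Not all would leave within a block, and not all because of an AE. But any who did would miss that block's CRQ, and a non-serious AE that led to withdrawal would stand on the card alone.

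**4. What remains usable.** Each block is one condition and the CRQ is given in each block, so for patients who complete the blocks there is a CRQ rating under anodal motor, cathodal cerebellar and sham stimulation. Card entries carry a date of onset. With dated blocks, an event can be assigned to a block and, after unblinding, to a condition, provided it is transcribed.

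**5. What a count would give.** If an event were counted and seen in 0 of 48 patients under a condition, the one-sided 95% upper bound on its rate would be 1 − 0.05^(1/48) ≈ 6%. With 36 patients (48 − 12), it would be 1 − 0.05^(1/36) ≈ 8%. These figures show the modest precision on offer; they do not measure the defect. For itching, redness and nausea, the plan as written provides no count from which such a bound could be stated.

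**The case against.** The strongest reply is that the trial already has a structured tolerability measure. The CRQ is a secondary outcome, is collected in every block and falls under the analysis by condition in 2.9. That stands. A reader might infer from 2.8 that no safety rating by condition is possible, and the documents do not support this: the CRQ supplies one for its own items. Nor does the abstract promise a table by condition; it says only that safety will be rated.

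A second reply is that the rule for non-serious AEs merely contrasts routes: such events do not go through the SAE form and its prompt notification. The card entry is dated and detailed, and a case report form or full protocol not shown here may provide for transcription. This is fair in part, since an article need not describe data entry. But the article does not stay silent. It names the card as the only place, and a later document that tabulated these events would have to depart from that wording.

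A third reply concerns scale. Section 2.6 calls skin irritation rare and 2.8 calls nausea seldom-occurring, so it would be wrong to say that all the uncovered events are the most expected ones. It would also be wrong to count skin irritation as an event separate from itching and redness, or to say that these events are irretrievably lost when dated card entries will exist. Finally, the main objective is hand dexterity. A reader might infer that serious harm could go unrecorded; 2.8 gives serious events their own form, so it could not on this account.

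**Conclusion.** The point holds in limited form. The closing sentence of 2.8 contradicts the abstract, 2.4.2 and 2.8 itself. Read as written, the rule for non-serious AEs leaves three gaps with no stated route into the study data:

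- itching, redness and nausea, which are three of the five mild events that 2.8 names;
- non-serious AEs in patients who leave before day 5 of a block;
- events other than pain later in the washout.

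The weight is minor to moderate. The primary outcome, the SAE record and the CRQ comparison of its own items are untouched. The conclusion rests on two assumptions: that the card rule is meant literally, and that the CRQ contains only the items listed in 2.4.2 and is completed only at the time given in 2.5. If a fuller document provides for transcription and tabulation, what remains is a wording conflict in 2.8.

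**What to change.** 1. Amend 2.8 so that non-serious AEs are also entered on a coded study form, using the items already required for the medical card, with the date and the block (and session, where the event falls within one). The form should not carry the stimulation condition; that is linked at analysis, so blinding is kept.
2. State that the number of patients with each AE will be tabulated by condition, alongside the CRQ. Say that an event in a washout is assigned to the block before it, and that patients who leave within a block are included in the table for that block.
3. Correct the closing sentence of 2.8 so that it agrees with the abstract, with the CRQ in 2.4.2 and 2.5, and with the SAE form. Name the CRQ there as the structured tolerability measure.

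The cost is one extra form and brief data entry. The information is already to be written on the card, so no extra visit or staff is needed. It is easier to set up before enrolment than to reconstruct from cards afterwards.

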### 2.9. Statistical Analysis

The statistical analysis will be performed using the SPSS software (IBM Corp. Released 2016. IBM SPSS Statistics for Windows, Version 24.0. Armonk, NY: IBM Corp). The primary and secondary outcomes will be analyzed using the same statistical approach. For all variables, the normality of data distribution will be tested using the Kolmogorov–Smirnov test. The homogeneity of variance will be tested using the Levene’s test. Depending on the data distribution, the scores obtained before and after all tDCS conditions will be compared using the repeated measures analysis of variance (ANOVA) or the Friedman test under six conditions: 2 times (before and after tDCS) × 3 stimulation conditions (anodal motor tDCS, cathodal cerebellar tDCS, and sham). When appropriate, the post hoc Dunn’s test will be applied. Two-tailed p-values less than 0.05 will be considered significant. Data will be presented as the mean ± the standard deviation or the median (1st and 3rd quartiles).

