## 2. Materials and Methods

This is a randomized, double-blind, crossover, and sham-controlled study. A crossover design has been chosen, so that each participant can act as his or her own control in an attempt to limit the inter-subject variability. In addition, such a design requires a smaller sample size compared to a parallel group design for the same statistical power [39]. However, one should acknowledge the limitations of this within-subject design, mainly, the time burden imposed on patients (longer participation time compared to the parallel-group design), and the possibility of a carry-over effect (e.g., potential neuroplastic effects induced by the preceding tDCS effects) or an order effect. The former effect cannot be formally ruled out, but was taken into consideration by including a washout period of 3 weeks between tDCS blocks, as done previously [40]. The latter effect could be controlled by counterbalancing the tDCS order among patients and could be statistically tested by adding the order as a covariate in the analysis of covariance (ANCOVA).

The study was approved by the institutional review board of the Lebanese American University, Lebanon (IRB registration #IRB00006954). All patients will voluntarily give their written informed consent prior to inclusion. The study will take place in conformity with the Declaration of Helsinki and its amendments.

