### 2.3. Sample Size, Randomization and Blinding Effectiveness

In the absence of published data on this topic, the statistical outcomes of this study can serve in understanding and guiding the therapies of altered dexterity in MS patients. Previous tDCS studies addressing dexterity in stroke patients adopted sample sizes between 10 and 19 and yielded statistical significance [59,60].

In the absence of sham-controlled studies on this matter, sample size calculation was performed using the G*Power Software (version 3.1.9.6 [61]). A 2 × 3 within-subjects repeated measures analysis of variance was considered, with the factor time (before and after each stimulation condition) and the factor stimulation condition (active cathodal cerebellar, active anodal motor vs. sham). Considering the predicted medium effect size (f = 0.25) and adopting a two-tailed significant difference of α = 0.05 and an estimated power of 80%, the sample size estimate is 36. Taking into consideration a dropout rate of up to 25%, a sample of 45 patients will be sufficient to observe significant effects. *N* = 48 was adopted to be able to counterbalance the order of conditions as will be explained below.

Randomization will be performed by a researcher who will not be in contact with patients. In the first step, six different sets of blocks will be assigned, and each contains four patients: (active cathodal cerebellar, sham, active anodal motor), set B (active cathodal cerebellar, active anodal motor, sham), set C (sham, active cathodal cerebellar, active anodal motor), set D (sham, active anodal motor, active cathodal cerebellar), set E (active anodal motor, sham, active cathodal cerebellar), and set F (active anodal motor, active cathodal cerebellar, sham). In the second step, each set will be split into two subsets according to the sham setup, so that two patients per set will receive sham over the motor cortex (setup similar to active condition), and the other ones will receive sham over the cerebellum (setup similar to active condition). The flow chart of the protocol is displayed in Figure 2. The evaluators will assess the patients before and after tDCS blocks and will be blind to the stimulation conditions. Patients will be blind to the stimulation condition.

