### 2.4. Description of the Clinical Evaluation

#### 2.4.1. Primary outcome: hand dexterity

The Nine-Hole Peg Test (9-HPT) will be administered by the evaluating physician to assess hand dexterity [5,62,63]. Briefly, patients will be trained to perform the test for five consecutive trials. The inter-trial interval will be 1 min. For each trial, the subject begins with the hand resting beside the pegboard. The experimenter initiates the trials with a verbal ready–steady–go command, and times the trial with a digital stopwatch. After training trials, another five trials will be done, recorded, and their sum will be calculated.

The dependent variable is the number of pegs per second computed based on nine pegs placed compared to the time needed to finish the test [63]. In case of inability to complete the test, the variable corresponds to the number of pegs placed divided by the time limit of the test (300 s).

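### A normality pre-test on the scores selects the primary test, and may without need replace the repeated measures ANOVA by a six-cell Friedman test that does not compare change between active and sham

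*Protocol article*

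**What the plan says.** Protocol article, section 2.9, sets a two-step rule. Step one: "For all variables, the normality of data distribution will be tested using the Kolmogorov–Smirnov test". Step two uses what that check shows to send the pre- and post-stimulation scores down one of two branches. The first branch is a repeated-measures ANOVA. The second is worded "or the Friedman test under six conditions: 2 times (before and after tDCS) × 3 stimulation conditions". The rule covers the primary outcome: "The primary and secondary outcomes will be analyzed using the same statistical approach".

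Three other places bear on it.

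- Section 2 justifies the crossover because "each participant can act as his or her own control in an attempt to limit the inter-subject variability".
- Section 2.3 bases the sample size on one model only: "A 2 × 3 within-subjects repeated measures analysis of variance was considered".
- Section 2.4.1 defines the primary variable: "The dependent variable is the number of pegs per second computed based on nine pegs placed compared to the time needed to finish the test". A patient who cannot finish is scored as pegs placed over the 300 s limit.

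Section 2.9 names no residuals, differences or contrasts as the object of the normality test. It does not say how many cells must fail before the Friedman test is used, or which Kolmogorov–Smirnov critical values apply.

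**The concern.** The treatment question is whether the D1-to-D5 change differs between each active condition and sham. In the 2 × 3 ANOVA this is the time-by-condition interaction, a comparison of changes within the same patient. A normality test on the scores asks something else: whether patients' levels are normally distributed across patients. Section 2.1 admits all three MS types, unilateral or bilateral clumsiness, and EDSS below 6.5, so a skewed spread of levels is plausible even where changes are well behaved.

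Two things are at stake. First, the patient mix may decide which primary test is run, although it says little about whether the ANOVA is sound. Second, the switch changes the hypothesis as well as the method. The six-cell Friedman test asks whether any of the six cells differ. A gain from D1 to D5 common to all conditions, sham included, can make it significant with no treatment difference.

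**Working it through.** **1. The plan's own figure.** With repeated measures in one group, λ = f²·N·m/(1 − ρ), with m − 1 and (N − 1)(m − 1) degrees of freedom. The inputs from section 2.3 are f = 0.25, α = 0.05 and 80% power. Taking m = 6 and ρ = 0 (ρ is not stated), N = 36 gives λ = 0.0625 × 36 × 6 = 13.5 on 5 and 175 degrees of freedom. This is the smallest N reaching 80%, so the stated 36 is reproduced. Other readings give 34 (m = 2, ρ = 0.5), 28 (m = 3, ρ = 0.5) or 19 (m = 6, ρ = 0.5). All are ANOVA calculations; no figure is given for the Friedman branch.

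**2. What cancels.** Write a score as patient level b plus a cell mean plus within-patient error. For one patient the treatment contrast is (active D5 − active D1) − (sham D5 − sham D1). The level enters as b − b − b + b = 0. Its distribution therefore has no influence on the contrast under this additive model, yet it is a main part of what a test on the scores sees.

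**3. How often the switch occurs.** The documents give no skew or correlation, so these are assumed: patient level normal (log-SD 0) or lognormal with log-SD 0.3 or 0.5, normal within-patient errors, within-patient correlation 0.5 to 0.85, pre-test at 5%, no effect, n = 48.

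| Reading of the pre-test | Trials switched to Friedman |
|---|---|
| Any of six cells fails, Lilliefors critical values | 22-85% |
| One cell tested, Lilliefors | 4-45% |
| Any of six cells, uncorrected critical values | 0.1-14% |

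At correlation 0.85 the any-cell Lilliefors rate is 22%, 60% and 84% for log-SD 0, 0.3 and 0.5. If all six cells had to fail, it would be 2% at log-SD 0.3.

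**4. Does rejection warn of a bad ANOVA?** At n = 36 and 48 (8,000 trials per setting, correlation 0.5 to 0.9, log-SD up to 0.7), the interaction test's type I error was 0.047-0.059 overall and 0.044-0.066 among the trials in which the pre-test rejected. With errors that scale with level (n = 36) it was 0.044-0.051.

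**5. What the Friedman test does.** At n = 36, with no treatment difference and an equal gain in all conditions of 0.2, 0.3 or 0.5 within-patient SD, the six-cell Friedman test rejects in 14%, 28% and 71%. The interaction test rejects in about 5%.

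**6. The two-stage rule as a whole** (n = 48, any-cell Lilliefors, no treatment difference, correlation 0.5 to 0.85):

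| Gain common to all conditions | Two-stage p < 0.05 | Interaction test |
|---|---|---|
| None | 4-6% | about 5% |
| 0.2 within-patient SD | 8-15% | about 5% |
| 0.2 total SD | 12-74% | about 5% |

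The unit matters. A gain of 0.2 total SD equals 0.2/√(1 − 0.85) = 0.52 within-patient SD at correlation 0.85, and 0.2/√(1 − 0.5) = 0.28 at correlation 0.5. The 74% belongs to correlation 0.85 with log-SD 0.5.

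**The case against.** Five objections have force.

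- **The switch is conditional.** A reader might infer that the ANOVA is dropped, or that all six cells are screened and one failure suffices. Section 2.9 says neither. Under uncorrected critical values the switch is uncommon. This stands, and it is why the rates are given as ranges.
- **The text does not say the scores are what is tested.** This is correct as to wording. But the sentence speaks of variables and the next of scores, and nothing points to residuals or differences. A fuller plan might specify the object of the test; the published rule does not.
- **The pre-test alone does not inflate error.** This stands. A reader might infer that the procedure loses its 5% level outright. With no shared gain it does not. The excess comes from the fallback's hypothesis and needs a gain common to all conditions. The documents give no size for one, and section 2.4.1 provides five training trials before the recorded ones. Those may reduce practice effects, but need not remove a placebo or session-related gain present in every block.
- **Score skew can carry some information.** If errors scale with level, the change contrasts are themselves non-normal: a Kolmogorov–Smirnov test on them rejected in 20-83% of simulated trials. The 300 s rule could act likewise. So it would be too strong to call the pre-test unrelated to the ANOVA's assumptions, although the ANOVA still held its level in those scenarios.
- **A low-powered pre-test might be thought a second harm, because it misses skewed scores.** That does not follow: if score skew matters little to the interaction test, missing it does little damage.

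It might also be said that Dunn's post hoc test rescues the Friedman branch. Pairwise comparisons of cells do not compare one change with another.

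**Conclusion.** The point holds in a limited form. Section 2.9 lets a normality test, on the natural reading applied to the scores, choose the primary test. That test mainly reflects between-patient spread, which the within-patient contrast largely removes. The alternative branch does not test whether change differs between active and sham. The ANOVA may therefore be replaced without need, and a significant result on the Friedman branch would not by itself support a treatment claim.

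The size is not fixed by the document. It depends on skew, within-patient correlation, the number of cells that must fail, the critical values used and the shared gain, all of which are assumed here. Exact cancellation needs additive patient effects. The documents do not support saying that the ANOVA will be discarded or that the 5% level is lost in all circumstances. They do support saying that the primary test should not depend on this pre-test, and the plan should be changed.

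**What to change.** In section 2.9:

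1. Remove the Kolmogorov–Smirnov selection step for the primary outcome.
2. Fix the time-by-condition analysis, that is active-versus-sham change, as the primary analysis in advance, whatever the distribution of the scores.
3. Judge normality by Q-Q plot on the model residuals or on the within-patient change contrasts.
4. Name in advance one rank-based or permutation sensitivity analysis on the same change contrasts, and state that it does not replace the primary test.

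The cost is wording in one section, with no new data or patients. The downside is some loss of power if the changes are heavy-tailed; the sensitivity analysis would help to show this.
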